### Secondary Analyses

The correlation between HRV and performance under caffeine will be evaluated with the Spearman's rank correlation coefficient.

Changes in tidal volume, blood pressure and epinephrine and norepinephrine blood concentration from baseline to post-treatment values will be compared between placebo and caffeine treatment using the Wilcoxon signed-rank test.

Changes in lactate blood concentration under treatment before and during performance testing will be compared between placebo and caffeine treatment using the Wilcoxon signed-rank test.

Changes in tidal volume and HRV under treatment before and after performance testing will be compared between placebo and caffeine treatment using the Wilcoxon signed-rank test.

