| Control Intervention (if applicable): | Placebo (mannitol) |
| Number of Participants with Rationale: | 30 participants in total (10 per each group of able-bodied, tetraplegic and paraplegic subjects): this study is a pilot study thus no power analysis was performed. |
| Study Duration: | 20 months |
| Study Schedule: | 01. May 2014: start of data collection  31. December 2015: end of data collection |
| Investigator(s): | [name]  Sports Medicine, Swiss Paraplegic Centre, [name], [contact], [contact] |
| Study Centre(s): | Single-center study: Swiss Paraplegic Centre Nottwil |
| Statistical Considerations: | For analysing the differences pre and post ingestion of caffeine within a subject, a Wilcoxon test will be used.  The correlation between HRV and performance under caffeine treatment will be evaluated with the Spearman’s rank correlation coefficient. |
| GCP Statement: | This study will be conducted in compliance with the protocol, the current version of the Declaration of Helsinki, the ICH-GCP or ISO EN 14155 (as far as applicable) as well as all national legal and regulatory requirements. |

study summary in local language can be provided here (German)

Die Herzfrequenzvariabilität (HRV) beschreibt die Varianz der Zeitintervalle zwischen den einzelnen Herzschlägen. Sie ist ein Parameter zur Bestimmung der Funktion des Sympathikus und Parasympathikus des autonomen Nervensystems. Diese beiden Komponenten haben antagonistische Aufgaben bei der Regulation der viszeralen Funktion des Körpers. Während der Sympathikus eine eher anregende Wirkung hat, hemmt der Parasympathikus.

Aus der Analyse der HRV resultieren zwei Komponenten, welche den zwei Systemen zugeordnet werden können. Die low frequency (LF) repräsentiert den Sympathikus während die high frequency (HF) dem Parasympathikus zugeordnet wird.

Je mehr also zum Beispiel der Sympathikus aktiviert ist, desto grösser ist der Anteil des LF- im Vergleich zur HF-Komponente. Mit der Analyse der HRV lassen sich so Aussagen über die sympathische-parasympathische Balance machen.

Bei querschnittgelähmten Personen ist durch die Verletzung des Rückenmarks auch das autonome Nervensystem betroffen. Davon ist, aufgrund seiner Austritthöhe entlang der Wirbelsäule bis ca. zum 6. Brustwirbel, nur der sympathische Anteil betroffen. Der Parasympathikus dagegen tritt auf Hirnstamm-Höhe aus und ist so nicht direkt von der Unterbrechung der Rückenmarks betroffen.

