## Clinical Evidence to Date

Since quite a while, caffeine is known as an ergogenic supplement for sports performance of able-bodied athletes. It was shown in several studies that caffeine enhances performance in short-term high-intensity exercise performance. Due to altered physical conditions after a spinal cord injury (decreased gut motility, impaired ANS, etc.) studies conducted with able-bodied subjects cannot be transferred one-to-one to wheelchair athletes. Therefore, it is compulsive to investigate the effects of caffeine on exercise performance also in wheelchair athletes. In a recent study [17] we were not able to show such performance enhancing effects in paraplegic elite athletes in a 1500m wheelchair exercise test. That`s why we want to go further to investigate the effects of caffeine on the level of the ANS.

It is known [34] that HRV is changed after the intake of caffeine in able-bodied subjects but it is also known that HRV changes after a spinal cord injury [13]. It was shown [19] that not all components of the HRV were detectable in spinal cord injured subjects. Some of these components were missing in some subjects. Therefore, it may be possible, that caffeine won`t alter the HRV because of these missing components. So, one first point is to understand, if HRV also changes after the intake of caffeine in tetraplegic and paraplegic subjects and if there are any differences between the three population groups (able-bodied subjects, tetraplegic and paraplegic subjects). It was also shown [15] that HRV is quite good reproducible in spinal cord injured subjects.

From another tetraplegic caffeine study [31] we have the information, that epinephrine and norepinephrine concentration did not increase after the intake of caffeine in tetraplegic subjects even if there was an increase in paraplegic subjects. If there is no increase of these catecholamines, it is possible that in tetraplegic patients no change in HRV and no change in exercise performance could be detected. Hence, it would be very interesting to see the correlation between the increase of the catecholamines, the change of the HRV and the effect of caffeine on exercise performance between our three different population groups.

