# STUDY OUTCOMES

## Primary Outcome

**Heart rate variability:** HRV difference between the measurement before the ingestion of caffeine compared to the measurement one hour after the ingestion of caffeine. This primary outcome gives us some further information about the effect of caffeine on the HRV and shows the differences between our three population groups.

**Exercise performance test:** We want to compare the power output between the two tests (placebo vs. caffeine) to know whether caffeine shows some ergogenic effects in the spinal cord injured population groups concerning arm crank exercise performance. To date, only one study examined exercise performance tests with the spinal cord injured population groups using caffeine as a supplementation [17]. These findings would provide some further information about caffeine supplementation in wheelchair sports.

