## Hypothesis

In order to investigate the effect of caffeine on the performance and the HRV, the two following primary hypotheses will be tested:

1. H_0_: m_1_ = m_2_ versus
   H_1_: m_1_ ≠ m_2_
   where m_1_ = performance (power output) under placebo
    m_2_ = performance (power output) under caffeine

   This hypothesis will be tested for the three subject groups (i.e. tetraplegic, paraplegic, able-bodied).
2. H_0_: m_1_ = m_2_ versus
   H_1_: m_1_ ≠ m_2_
   where m_1_ = change in HRV from baseline to post-treatment under placebo treatment
    m_2_ = change in HRV from baseline to post-treatment under caffeine treatment

   This hypothesis will be tested for the three subject groups (i.e. tetraplegic, paraplegic, able-bodied).

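### The planned HRV–performance correlation uses the caffeine session alone, with performance as a raw power level, so it cannot show whether a man's HRV response to caffeine tracks his performance response

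*Protocol*

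**What the plan says.** Section 11.4.3 (Secondary Analyses) plans one correlation: "The correlation between HRV and performance under caffeine will be evaluated with the" Spearman coefficient. The synopsis, under Statistical Considerations, has it almost word for word: "The correlation between HRV and performance under caffeine treatment will be evaluated with the" same coefficient. Neither place brings in a placebo value or a difference between sessions.

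The remaining analyses in section 11.4.3 are built differently. Each takes a change and contrasts the two treatments, for example: "Changes in tidal volume and HRV under treatment before and after performance testing will be compared between placebo and caffeine treatment".

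Section 3.4 (Clinical Evidence to Date) describes the relation of interest as the "correlation between the increase of the catecholamines, the change of the HRV and the effect of caffeine on exercise performance". Section 5.1 (Primary Outcome) defines the performance effect as a comparison of power between the placebo and caffeine tests. Section 11.1 (Hypothesis) defines the HRV effect by setting the "change in HRV from baseline to post-treatment under caffeine treatment" against the same change under placebo. Section 9.3 (Procedures at each visit) has every man complete both sessions, with a single 3-minute test in each, after the capsules.

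**The concern.** The relation in section 3.4 is between responses: does the man whose HRV shifts more with caffeine also gain more power from it? A correlation confined to the caffeine session asks something else, namely whether men with a given HRV value (or HRV change) that day also produced more power that day. Power on an arm crank differs between men for reasons present with or without caffeine, such as fitness, age (18 to 60 is allowed) and, among the tetraplegic men, lesion level from C5 to C7.

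Two things are at stake. A true link between responses would be diluted by these stable differences. If HRV also enters as a level, the same differences can produce a correlation where the responses are unrelated. Section 11 counts any p-value below 0.05 as significant although several hypotheses are tested, so such a result would be reported as significant. This is the only planned analysis that relates HRV to performance.

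**Working it through.** **What the variables can be.** The documents give no figure for this correlation, so there is none to reproduce.

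- *Performance under caffeine.* Section 9.3 has one 3-minute test per testing day, after ingestion. The familiarisation run is on another day and is not named as a baseline. Performance is therefore a power level.
- *HRV under caffeine.* Two readings are open. It may be the post-dose level, or the change from baseline within the caffeine session, which is how sections 5.1 and 11.1 describe the HRV outcome. The second reading still includes whatever change the same hour would have brought under placebo.

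**Model (assumptions).** Value under caffeine = stable level + caffeine response. Let k be the level SD divided by the response SD, ρL the correlation of levels, ρR the correlation of responses, and e the error SD per measurement divided by the response SD. None of these is in the documents. From the protocol: 10 men per group, groups analysed separately (11.4.1), two-sided 0.05 (11). The Spearman critical value at n = 10 is 0.648.

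Underlying correlations:

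- Both as levels, no error: (k²ρL + ρR)/(k² + 1)
- HRV as within-session change, power as level, no error: ρR/√(k² + 1)
- Caffeine-minus-placebo differences: ρR/√[(1 + 4e²)(1 + 2e²)], because the HRV double difference uses four recordings and the power difference two tests.

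**Case 1: levels correlated 0.6, responses unrelated, no error.**

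- Both as levels: k = 2 gives (4 × 0.6)/5 = 0.48; k = 5 gives (25 × 0.6)/26 = 0.58. Simulated mean Spearman is 0.42 to 0.51, significant in about 24 to 36% of groups.
- HRV as change: 0, significant in about 5%.
- Differences: 0, significant in about 5%.

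**Case 2: responses correlated 0.7, levels unrelated, no error.**

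- Both as levels: k = 2 gives 0.7/5 = 0.14; k = 5 gives 0.7/26 = 0.03. Significant in about 5 to 6%.
- HRV as change: k = 2 gives 0.7/√5 = 0.31; k = 5 gives 0.7/√26 = 0.14. Significant in about 6 to 12%.
- Differences: 0.70, significant in about 55%.

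**Case 2 with measurement error, difference-based analysis.**

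| e | Underlying correlation | Groups significant |
|---|---|---|
| 0 | 0.70 | about 55% |
| 0.25 | 0.7/√(1.25 × 1.125) = 0.59 | about 38% |
| 0.5 | 0.7/√(2 × 1.5) = 0.40 | about 18% |
| 1 | 0.7/√(5 × 3) = 0.18 | 7–8% |

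**Precision at n = 10.** Suppose a coefficient of 0.5 is observed. With Fisher's approximation, atanh(0.5) ± 1.96/√7 = 0.549 ± 0.741, so the 95% interval runs from about −0.19 to 0.86. Even the corrected correlation will be imprecise.

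**The case against.** The best defence has four parts.

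1. *The protocol does not say levels.* A reader might infer that both variables enter as levels and that a spurious fitness correlation will follow. The wording does not settle this. On the change reading, Case 1 shows no spurious correlation. What remains is that power is still a level and no placebo contrast enters, so a true response link is still mostly missed.

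2. *No objective is breached.* A reader might take the omission of catecholamines as a failure to meet an objective. Sections 4.1 to 4.4 list no correlation, with or without catecholamines. The response-to-response relation appears only in the background, where it is called interesting. This part stands; adding catecholamines is optional.

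3. *No mechanistic claim is planned.* A reader might infer that a positive coefficient would be presented as caffeine's mechanism. The documents attach no such conclusion to it. This is a secondary analysis in a pilot, and the primary tests are paired placebo contrasts. That also stands and limits the weight of the point.

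4. *The remedy is noisy.* A power of 55% assumes error-free measurement. When error is as large as the response, the difference-based analysis detects little more than chance. This stands too. The case for the change is that it targets the right quantity; a reliable gain in power cannot be promised.

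The exact definition of variables is often left to a statistical analysis plan. Here, however, the protocol itself fixes, in two places, that the correlation is under caffeine.

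**Conclusion.** The point holds in a limited form. On either reading of HRV, the correlation in section 11.4.3 and the synopsis omits the placebo session and uses power as a level, so it cannot show whether HRV response tracks performance response. That follows from the design and needs no assumed figures.

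The size does rest on assumptions. The 24 to 36% of falsely suggestive groups applies only to the level reading, with levels correlated 0.6, k from 2 to 5 and no measurement error. For a true response correlation of 0.7, the planned analysis detects about 5 to 6% (level reading) or 6 to 12% (change reading) without error. The corrected one detects between about 55% and 7–8%, depending on error. The correction is worth making but does not bear on the primary conclusions.

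**What to change.** In section 11.4.3 and the synopsis, replace the sentence with wording such as: *Within each subject group, the caffeine-minus-placebo difference in HRV change from baseline (for the HRV parameter and posture used in the primary analysis) will be correlated with the caffeine-minus-placebo difference in power output, using Spearman's coefficient with a 95% confidence interval; this analysis is exploratory.* The corresponding catecholamine difference may be added, also as exploratory. Each addition means further unadjusted coefficients per group, so keep the list short.

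The cost is one sentence in each of two places. The crossover already supplies every value, with no extra visit, sample or participant. The drawback is the noise of differences at n = 10, so the result should be read as an estimate with a wide interval and a non-significant coefficient should not be taken as absence of a link.

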| Objective(s): | In general, we are interested in the differences between the heart rate variability before and after caffeine supplementation and if exercise performance is enhanced using this type of supplementation. Another objective is to see whether there are differences between abled-bodied and disabled subjects as subjects with spinal cord injury have an impairment of the autonomic nervous system. |
| Outcome(s): | Primary outcome parameters are differences in heart rate variability and power output in the exercise performance test between caffeine and placebo trial. Secondary outcome parameters are epinephrine and norepinephrine concentration before and after caffeine supplementation, heart rate, tidal volume, lactate concentration before and after the exercise testing, as well as rating of perceived exertion after the exercise performance test. |
| Study design: | Randomised, double-blind, placebo controlled trial (RCT); pilot study |
| Inclusion / Exclusion criteria: | Inclusion: healthy, non-smoker, minimal 3x45 min physical activity per week, tetraplegic (C5 to C7) or paraplegic (sub Th8), AIS A, termination of first rehabilitation and more than 6 months after trauma.  Exclusion: drugs or supplements which influence heart rate variability, diabetes |
| Measurements and procedures: | Heart rate variability (HRV) is measured using a Polar heart rate monitor. After a 10min rest, HRV is measured during a 5 min phase in supine position and afterwards during a 6 min time period in sitting position. These measurements are conducted before the ingestion of the supplement, before the exercise performance test and after the exercise performance test.  Epinephrine and norepinephrine concentrations are measured before supplementation and one hour after supplementation (venous blood withdrawal).  Resting tidal volume is measured during the measurements of HRV.  Power output during the 3 min exercise performance test is analysed.  Lactate concentration is measured before and after the exercise performance testing taking a capillary blood sample.  Blood pressure is measured immediately before every HRV measurement.  Rate of perceived exertion is measured after the warm up and after the exercise performance test. |
| Study Product / Intervention: | Caffeine: 6 mg/kg body mass dosage, supplement will be ingested 1 hour before the exercise performance test respectively 45 min before the HRV measurement. |

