## Secondary Outcomes

**HRV:** As a secondary outcome we try to compare HRV baseline measurement with the measurement after the exercise test. As we know from previous data, HRV should be altered after an exercise performance and could be influenced by the ingestion of caffeine.

**Catecholamines:** We will compare epinephrine and norepinephrine concentrations before the ingestion of any supplement with the concentrations one hour after the ingestion of the supplements. As some previous studies showed no effect of caffeine on epinephrine and norepinephrine concentrations in tetraplegic patients, it will be very interesting to see these results and to compare it to our HRV and performance exercise testing.

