After these 40 min, the second HRV measurement starts. The process of this measurement is exactly the same as for the first HRV measurement. They lay down for a 10 min rest with blood pressure measurement after 9 min. Afterwards again a 5 min HRV measurement in supine position and a 6 min measurement in sitting position will be performed. Tidal volume is measured during this HRV measurement.

When this second HRV measurement session is finished, a second blood withdrawal has to be taken. That means, one hour after the ingestion of either placebo or caffeine, catecholamines are analysed for a second time. After blood sampling, the warm up can start. After the standardised warm up lactate concentration of the blood is analysed taking 10 µl of blood from the earlobe using a blood lactate analyser (Biosen, EKF diagnostic, Cardiff, Great Britain) for analysis. The subject will be asked to evaluate the warm up by rating of the perceived exertion (following the Borg scale from 6 to 20). Then the 3 min exercise test can start. During this test, respiratory parameters will be measured using a device to measure oxygen consumption (MetaMax 3B,Cortex Biophysik GmbH, Leipzig, Germany). Just after having finished these 3 min of exercising, for a second time lactate concentration will be measured and again they have to rate the exertion using the Borg scale (6 to 20).

After a short 5 min break the third HRV measurement starts. Again HRV will be measured during a 5 min time in supine position and a 6 min time in sitting position. Tidal volume will be measured during the whole HRV measurement. With this HRV measurement the first test session is finished and a second test session will be conducted at least more than two days later in a randomised order.

The first visit will take 30 min. The screening and familiarization trial will be finished in around 75 min. For the two test sessions the subject has to be at the Sports Medicine for about 90 min.

In the following chart, the two 90 min test sessions are visually displayed.

[figure not shown]

As we know from previous studies conducted with disabled subjects, the level of the lesion is one critical point. Therefore, we tried to include subjects with almost the same lesion level and sensory and motor complete lesion. This could help us to have more homogenous groups of different populations.

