**HRV:** The values of HRV comparing before and after ingestion are measured 2 times at each of the testing day. This two measurements will be assessed with the following procedure: the subject is relaxing supine on a couch for 10 min. Then he starts breathing with a predefined breathing frequency of 15 breaths per minute. The assessment with fixed breathing rate takes 5 min in supine and 6 min in sitting position. The first baseline measurement takes place at the beginning of the experiment, the second after ingestion of caffeine or placebo followed by a 40 min break. For assessing the HRV we use a Polar heart rate monitor (Polar, Kempele, Finland) and a heart rate belt which transfers the data directly to the watch.

**Exercise performance:** We want to measure the power output during a 3 min all out performance test on an arm crank ergometer (Angio V2, Lode, Groningen, Netherlands). This test takes place after the ingestion of caffeine or placebo followed by a 40 min break and a short warming up.

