### Assessment of secondary outcomes

**HRV:** For comparing the HRV baseline values with the values after the performance test, we use the results of the first HRV measurement (see above 9.2.1.) as baseline values. Then we perform a second measurement after the 3 min performance test followed by a 5 min break. For this measurement the subjects breaths with fixed rate in supine position on a couch for 5 min and then gets up with his upper body, sitting for 6 min with the same breathing rate. Meanwhile the HRV is measured by a Polar heart rate monitor (Polar, Kempele, Finland) and a heart rate belt. The data is transferred directly to and saved on the watch. The data will later be analysed on the computer with the Kubios Software (University of Eastern Finland, Kuopio, Finland).

**Catecholamine:** Epinephrine and norepinephrine are stress hormones and their concentration will be assessed twice during the testing procedure. The first one after the first HRV measurement as a baseline value and the second about 60 min after ingestion of the capsules. The subject is sitting up and the blood is taken at the crook of the arm. The blood samples are then frozen and will be later analysed by a laboratory.

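### The secondary HRV outcome is defined against the pre-dose recording, but Section 11.4.3 most naturally tests it against the post-dose, pre-exercise recording

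*Protocol*

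**What the plan says.** **Outcome.** Section 5.2 (Secondary Outcomes) states: "As a secondary outcome we try to compare HRV baseline measurement with the measurement after the exercise test". Section 9.2.2 fixes the reference for this outcome: "we use the results of the first HRV measurement (see above 9.2.1.) as baseline values". Section 9.2.1 places that recording in time: "The first baseline measurement takes place at the beginning of the experiment". Under Section 6.1 the capsules are swallowed only after this recording and the first venous sample.

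**Other recordings.** The second recording follows dosing and precedes exercise: "After these 40 min, the second HRV measurement starts" (Section 6.1). The third follows the 3 min test: "After a short 5 min break the third HRV measurement starts" (Section 6.1).

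**Analysis.** Section 11.4.3 (Secondary Analyses) plans, with a Wilcoxon signed-rank test: "Changes in tidal volume and HRV under treatment before and after performance testing will be compared between placebo and caffeine treatment". No other planned comparison of caffeine with placebo uses the post-exercise recording.

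**Rest before recording.** The synopsis (Measurements and procedures) says "After a 10min rest, HRV is measured during a 5 min phase in supine position", and applies this description to all three time points, including the one after exercise. Sections 6.1 and 9.2.2 give a 5 min break before the third recording, and Section 9.3 uses those 5 min for the transfer back to the couch.

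**The concern.** The outcome sections and the analysis section appear to use different reference recordings. HRV1 is free of any treatment effect. HRV2 is taken after the capsules, so under caffeine it already carries whatever caffeine does to resting HRV. Subtracting HRV2 therefore removes from the result any part of the caffeine effect that is present both before and after exercise.

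What is at stake is the interpretation of one secondary outcome. A null result from the Section 11.4.3 test could be reported as showing that caffeine does not alter HRV after exercise. The same result would be expected if caffeine altered HRV by the same amount before and after exercise.

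**Working it through.** The documents give no figure for this point, so there is nothing to reproduce. The check has three steps.

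**1. Which recording is the reference in Section 11.4.3?**

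- HRV1 precedes ingestion, so it fits poorly with a change described as occurring under treatment.
- Where Section 11 means the pre-dose reference, it says so by naming baseline. It does this for the primary HRV hypothesis (11.1, 11.4.2) and, in 11.4.3 itself, for tidal volume, blood pressure and catecholamines. The post-exercise sentence does not name baseline.
- The preceding sentence, on lactate, uses parallel wording. Its earlier sample is taken after the warm-up and hence after dosing (Sections 5.3, 6.1, 9.2.3). This supports the reading only weakly, because no pre-dose lactate sample exists.

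The most natural reading is HRV3 - HRV2.

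**2. What does each contrast estimate?**

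Let c2 and c3 be the caffeine-minus-placebo shifts at HRV2 and HRV3, with equal expected pre-dose values in the two sessions.

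- Primary HRV contrast (11.1): (HRV2 - HRV1) caffeine minus (HRV2 - HRV1) placebo, expectation c2.
- Secondary outcome as defined (5.2, 9.2.2): (HRV3 - HRV1) caffeine minus (HRV3 - HRV1) placebo, expectation c3.
- Test as written (11.4.3): (HRV3 - HRV2) caffeine minus (HRV3 - HRV2) placebo, expectation c3 - c2.

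Since HRV3 - HRV2 = (HRV3 - HRV1) - (HRV2 - HRV1), the planned contrast equals, for each man, the defined secondary contrast minus the primary contrast. The two versions agree in expectation only if c2 = 0, that is, if caffeine does not shift resting HRV. Such a shift is what the primary HRV hypothesis is set up to detect.

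For example:
- sustained effect, c3 = c2: defined c2, planned 0;
- effect halved, c3 = 0.5 c2: defined +0.5 c2, planned 0.5 c2 - c2 = -0.5 c2;
- effect gone, c3 = 0: defined 0, planned -c2.

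**3. Illustration by simulation.**

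The Section 11.4.1 minimum of 10 data sets per group was used, with a two-sided Wilcoxon signed-rank test at 0.05 and 4000 runs. The SD of 1 per recording is an assumption, as are c2 and c3, because the protocol gives no HRV figures. Each contrast combines four independent errors, so its SD is √4 = 2.

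| c2, c3 | Mean, defined | Mean, planned | Rejection, defined | Rejection, planned |
|---|---|---|---|---|
| 0, 0 | 0.0 | 0.0 | 5% | 5% |
| 1, 1 | 1.0 | 0.0 | 28% | 5% |
| 2, 2 | 2.0 | 0.0 | 79% | 5% |
| 2, 1 | 1.0 | -1.0 | 28% | 28% |
| 2, 0 | 0.0 | -2.0 | 4% | 77% |
| 0, 2 | 2.0 | 2.0 | 79% | 78% |

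With a sustained effect the planned test rejects at about its nominal level however large the effect is. The rejection rates depend on the assumed SD. The means follow from the algebra.

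**The case against.** **The reference may be ambiguous rather than wrong.** Section 11.4.3 never names the second recording. HRV1 also precedes the performance test. In Section 11.1 the protocol speaks of a baseline-to-post-treatment change under placebo or caffeine treatment, so there the phrase covers a whole session, pre-dose value included. A reader might infer that the defined outcome is certainly never tested. The documents do not support certainty: HRV3 - HRV2 is the likely reading, not the only possible one. The point survives either way, because the reference has to be stated and has to match Sections 5.2 and 9.2.2.

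**HRV3 - HRV2 is a sensible quantity.** A reader might infer that the planned test has the wrong sign or gives a wrong answer. That is true only if its result is read as the Section 5.2 outcome. As a measure of how caffeine modifies the HRV response to exercise, c3 - c2 has the right sign. The rationale in Section 5.2, that HRV changes after exercise and caffeine might influence it, could even be read as asking for this. But Section 9.2.2 explicitly names the first recording as baseline, so it is not the outcome the protocol defines. Redefining the outcome would also make the text consistent, but it would change the stated question.

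**Tidal volume.** The same sentence in Section 11.4.3 covers tidal volume, so a reader might infer the same mismatch there. There is none. Section 5.3 defines that outcome as before ingestion versus one hour after, and 11.4.3 already tests it as a change from baseline.

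**Rest before HRV3.** A reader might infer that the 10 and 5 min versions bias caffeine against placebo, or let sites measure different endpoints. This is a single-centre study, and Section 9.3 makes the second testing day the same as the first. An interval common to both sessions does not by itself bias a within-subject comparison. The 10 min version for HRV3 appears only in a condensed synopsis sentence. This is a minor inconsistency to reconcile.

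**Conclusion.** The point holds for the secondary HRV outcome. Sections 5.2 and 9.2.2 fix HRV3 against HRV1. Section 11.4.3, on its most natural reading, tests HRV3 against HRV2. The estimates differ by exactly c2, the effect of caffeine on resting HRV. The planned test therefore has an expected value of zero for a sustained caffeine effect of any size. It can also show a difference when post-exercise HRV does not differ between treatments.

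The conclusion assumes comparable pre-dose HRV in the two sessions and shifts that add to the recording. The size of c2 and c3 is unknown, so the practical loss cannot be given as a number.

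The reach is limited. The primary HRV analysis uses HRV1 and HRV2 with the reference clearly stated and is unaffected. The trial is a pilot, the outcome is secondary, and both contrasts can be computed from the recordings taken. The correction should still be made before analysis, because the protocol fixes two different contrasts under one outcome and an analysis plan cannot follow both.

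**What to change.** 1. In Section 11.4.3, state that the secondary HRV outcome is tested as HRV3 - HRV1 under caffeine versus HRV3 - HRV1 under placebo, with the Wilcoxon signed-rank test in each subject group, as Sections 5.2 and 9.2.2 define it.
2. Keep HRV3 - HRV2 as a separately labelled contrast describing how caffeine modifies the exercise response, and name both recordings explicitly.
3. Leave the tidal-volume outcome as Section 5.3 defines it.
4. As a minor correction, reconcile the rest before HRV3 between the synopsis and Sections 6.1, 9.2.2 and 9.3.

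The cost is a few sentences. No visit, recording or participant is added.
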